To help them achieve and maintain the weight goal, participants also will be given a goal for daily calories. A moderate reduction of caloric intake by 500-1000 kcal/day has been shown to produce clinically significant weight loss over time and is a safe and achievable goal for most people [27]. Of note, the calorie goals will be given as a means to achieve and maintain the weight goal, rather than as a goal in and of itself. Therefore, if a participant consumes more than the assigned calorie goal, but is achieving the weight goal, there is no need to focus on further reductions. Participants will be encouraged to gradually achieve the calorie goals through portion control, choices of low-energy and nutrient-dense meals and snacks, healthy food preparation techniques, and careful selection of restaurants, including fast food, and of the items offered. Participants also will be advised to: (1) lower saturated fat intake to <10% of caloric intake, (2) lower cholesterol intake to <300 mg/day, (3) consume a high plant-based diet that includes a variety of vegetables, beans, whole grains, low-fat dairy products, and whole fruits, and (4) reduce intake of high glycemic index carbohydrates.

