##### Intensive Stage

The Intensive stage of the BE WELL intervention is adapted from the Group Lifestyle Balance (GLB) program™ [66]. The GLB program is based on the highly successful Diabetes Prevention Program [57] and includes 12 weekly small group sessions. Each session follows a similar structure and includes five curriculum components: 1) measurement and recording of weight, 2) review of self-monitoring records and progress, 3) identification of personal barriers to weight loss and activity and potential solutions, 4) presentation of a new content area, and 5) goal setting and action plans for next week. In BE WELL, the GLB Manual of Operations will be closely followed, except for the addition of a food tasting activity as part of the check-in process and a 30-minute segment of physical activity demonstrations and practices at the end of each session. The food tasting activities are aimed at increasing participant experience with healthy food choices, encouraging them to try new foods that they might not normally try on their own, and stimulating a social, fun and engaging environment. The physical activity demonstrations and practices are aimed at increasing participant awareness of physical activity intensity, experiencing various moderate-intensity activities that are safe and that they can easily incorporate into their daily lives, and increasing participant confidence. As part of these supervised exercises, participants will learn how to recognize exercise-induced bronchospasm based on symptoms and peak flow meter readings and the appropriate prophylaxis and treatment. In BE WELL, participants will be given a pedometer and start using it to record their daily steps in week 1, as opposed to starting this in week 10 as in the original GLB program. Furthermore, BE WELL participants will attend an additional group session focusing on the latest evidence that came out after the GLB program on high-carbohydrate and high-fat/high-protein dietary approaches to weight loss to complement the program's emphasis on low-fat diets. The 13 group sessions of 90-120 minutes each will be delivered by a nutrition health educator and a fitness instructor over a 4-month period.

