#### Statistical analysis

The primary hypothesis compares Juniper ACQ scores between the WL and UC arms at 12 months using an intent-to-treat analysis. Linear mixed modeling, using SAS PROC MIXED [67] will test time and group interactions to assess whether within-subject change in Juniper ACQ scores differs by condition (equation 3).(3)

Due to randomization, the distributions of baseline values on the dependent variable (Y_0_) and baseline covariates (X_i _where i = 1 to k) should be similar between treatment arms and thus not bias the analysis. Nonetheless, to the extent they are associated with the outcome, their inclusion in the model will account for otherwise unexplained variation and hence increase the efficiency of the analysis. In addition, their inclusion will guard against imbalance in the distributions of these covariates between treatment arms, which can still occur despite randomization. a, g, and δ represent the random effects caused by clustering of patients with physicians and, in turn, physicians within clinics, and by blocking of patients within medical centers. ε takes into account the correlation of repeated measures within subjects.

The same analysis strategy is appropriate for evaluating secondary aims where the hypotheses are identical but with different outcome measures (e.g., lung function, asthma-specific QoL, asthma-related HCU). The longitudinal effects of the intervention will be assessed using the same model, except that the focus is comparisons within the intervention arm at different time points. Analyses will also be conducted to examine whether there is a dose-response relationship between intervention adherence and outcome, where dose is defined in terms of number of group sessions attended, number of self-monitoring logs kept, average daily intakes of calories and fat, and average number of minutes of physical activity per week.

The primary analyses will be intention-to-treat. Secondary per-protocol or as-treated analyses will be performed to help elucidate the primary findings. For subjects with missing data at follow-up, we will conduct and report on sensitivity analyses in which several previously recommended approaches for handling missing data in longitudinal trials will be used, e.g., multiple imputation and the pattern-mixture model [68].

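### The adherence dose-response analysis scores diet by level of calorie and fat intake, whereas the intervention targets a calorie reduction and saturated fat as a share of calories, so the measure mixes habitual intake with adherence

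*Protocol article*

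**What the plan says.** The Statistical analysis section plans to examine "whether there is a dose-response relationship between intervention adherence and outcome". It then fixes the exposure: "where dose is defined in terms of number of group sessions attended, number of self-monitoring logs kept, average daily intakes of calories and fat", and adds average weekly minutes of physical activity. The diet items refer to no baseline value, assigned goal or share of energy.

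Evidence-based Intervention Goals describes what participants are asked to do. On calories, "participants also will be given a goal for daily calories", and the supporting evidence is for a reduction: "A moderate reduction of caloric intake by 500-1000 kcal/day has been shown to produce clinically significant weight loss over time". Calories are presented as a means to the weight goal: "if a participant consumes more than the assigned calorie goal, but is achieving the weight goal, there is no need to focus on further reductions". The one numeric fat target is to "lower saturated fat intake to <10% of caloric intake". The same section says that the weight-loss and activity goals are common to all participants; it does not say this of calories.

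Elsewhere diet is treated as change. The Abstract and the Aims name change in nutrient intake or diet composition as a potential mediator, and Potential Mediators speaks of changes in BMI, physical activity and diet. Table 2 schedules three-day food records at baseline, 6 and 12 months.

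**The concern.** A measure of adherence should rank participants by how closely they followed what they were asked to do. If the request is to eat less than before, intake at follow-up answers another question: how much the person eats now. That depends on the reduction achieved and on habitual intake, which varies with sex and body size. The trial expects 67% women and admits BMI from 30.0 to 44.9 kg/m², so habitual intake is likely to differ between participants.

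The fat item has a similar mismatch. The numeric target is saturated fat as a share of calories, while the dose item is fat without qualification.

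At stake is how a supportive analysis is read. A flat gradient could arise because the exposure is diluted by habitual intake. A sloped one could arise because habitual intake, or something related to it, is itself associated with asthma control. In neither case could the reader tell whether more adherence went with better control.

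**Working it through.** The protocol states no figure on this point, so there is none to reproduce. The check has two parts.

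**1. Target against measure**

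| Component | What the intervention asks | How dose is scored | Match |
|---|---|---|---|
| Sessions, logs | Attend, self-monitor | Counts | Yes |
| Activity | At least 150 min/week, same for all | Average min/week | Yes |
| Calories | Reduction, with an assigned goal | Average daily intake | No |
| Fat | Saturated fat below 10% of calories; low-fat emphasis in the curriculum | Average daily intake of fat | Partly |

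**2. How far an intake level reflects the reduction**

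Write follow-up intake as F = B - R, with B the baseline intake and R the achieved reduction, taken as independent. Let SDb be the standard deviation of baseline intake within sex, SDr that of the reduction, D the male-female difference in baseline intake, and 0.67 the proportion of women (from Eligibility Criteria). Then:

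- Var(B) = SDb² + 0.67 × 0.33 × D²
- Var(F) = Var(B) + SDr²
- corr(F, R) = -SDr / √Var(F)
- corr(F, B) = √Var(B) / √Var(F)
- corr(F, female) = -D × √(0.67 × 0.33) / √Var(F)

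The documents give no value for SDb, SDr or D. Assumed ranges are SDb 300 to 600, SDr 200 to 400 and D 0 to 600 kcal/day, three values of each, giving 27 combinations. Worked cases:

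- SDb 300, SDr 400, D 0: √(90,000 + 160,000) = 500; corr(F, R) = -400/500 = -0.80; corr(F, B) = 300/500 = 0.60.
- SDb 400, SDr 300, D 0: √(160,000 + 90,000) = 500; corr(F, R) = -300/500 = -0.60; corr(F, B) = 400/500 = 0.80.
- SDb 600, SDr 200, D 600: Var(B) = 360,000 + 0.2211 × 360,000 = 439,596; Var(F) = 479,596, root 692.5; corr(F, R) = -200/692.5 = -0.29; corr(F, B) = 663.0/692.5 = 0.96.

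| SDb | SDr | D | corr with reduction | Share of variance | corr with baseline | corr with female sex |
|---|---|---|---|---|---|---|
| 300 | 400 | 0 | -0.80 | 64% | 0.60 | 0 |
| 400 | 300 | 0 | -0.60 | 36% | 0.80 | 0 |
| 400 | 300 | 400 | -0.56 | 32% | 0.83 | -0.35 |
| 300 | 200 | 600 | -0.44 | 19% | 0.90 | -0.62 |
| 600 | 200 | 600 | -0.29 | 8% | 0.96 | -0.41 |

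A simulation of all 27 combinations gave correlations with the reduction from -0.29 to -0.80 (8% to 64% of variance), with baseline intake from 0.60 to 0.96, and with female sex from 0 to -0.62. Baseline intake was the stronger correlate in most combinations, though not all.

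Two limits apply. Independence of B and R is an assumption: if people who eat more also cut more, the link between F and R weakens further. And, without measurement error, F and R carry the same information once B is held fixed. This is why adjustment for baseline intake answers most of the concern.

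**The case against.** The strongest reply is that this is one sentence in a condensed article. It names the domains of dose and may not be the full derivation. Baseline adjustment is not excluded, no unit is given for fat, and the main model carries baseline covariates. That has weight, but the sentence does state a definition, and it states a level. The section does not say which covariates enter the dose-response analysis, and baseline intake is not among the balancing factors listed under Randomization and Blinding (age, sex, race/ethnicity, BMI, ACQ score). Adjusting for sex would remove only the sex component: the combinations with D = 0 still give -0.32 to -0.80.

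A second reply concerns fat, and it stands in part. The added session on "high-carbohydrate and high-fat/high-protein dietary approaches to weight loss" is meant to complement a curriculum that emphasizes low-fat eating and is otherwise closely followed. Total fat is therefore a relevant marker. A reader might infer that someone who adopts a higher-fat approach taught in class would be scored as non-adherent. The text does not support this: the session presents evidence on several approaches, and nothing says that participants are advised to adopt one.

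A reader might also infer that calorie goals are set person by person. The article speaks of an assigned goal and a reduction, which makes this plausible, but it does not say how the goal is set.

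Finally, the analysis is supportive and non-randomized, and attendance and log counts are untouched. This stands and limits the importance of the point.

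**Conclusion.** The point holds as a mismatch between the stated dietary dose and the stated dietary targets. A level of calorie intake mixes habitual intake with adherence, and unqualified fat intake does not capture the saturated-fat target. How much this dilutes the gradient depends on intake standard deviations that the documents do not give; under the assumed ranges the level shares between 8% and 64% of its variance with the achieved reduction.

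It would be tempting to conclude that the dose tracks sex and body size instead of adherence. That is not shown. In every combination examined the level still carries information on the reduction, and its correlation with sex is zero where no sex difference is assumed.

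The consequence is confined to the interpretation of one part of a secondary analysis. The primary intention-to-treat comparison, the sample size and the error rate are unaffected. The correction is worth making because it is cheap.

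**What to change.** In the dose-response analysis, define the calorie component as change in average daily intake from the participant's own baseline food record, or model follow-up intake with baseline intake as a covariate. Add saturated fat as percent of calories and keep total fat beside it, given the low-fat emphasis of the curriculum.

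Activity minutes can stay as they are: the goal is common to all, so rescaling to 150 minutes would leave a linear gradient unchanged. Intake minus the assigned goal is not recommended. Assigned goals are not listed in Table 2 or under Process Measures, and the protocol itself does not treat eating above the goal as a lapse when the weight goal is being met. Change from baseline does not fully resolve that allowance either, so the report should say that a smaller calorie cut is not necessarily poor adherence.

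The cost is a few derived variables from food records already planned. The drawback is that change scores from three-day records are noisier than a single level; the baseline-adjusted form mitigates this, although error in the baseline record leaves some habitual-intake effect in place.

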### Data Management

All study data will be entered into computerized data files utilizing: 1) Microsoft Access for participant tracking and intervention data entry, 2) Vovici's survey software (Dulles, VA) for self-administered questionnaires and entry of clinical measurements, 3) the Nutrition Data System for nutrient analysis based on three-day food records, and 4) a custom-designed web application for seven-day physical activity recall data entry. Research assistants (blinded to participant group assignments) will review participant responses on questionnaires with participants present, and skipped or incorrectly addressed items will be brought to the participant to correct. All of the data entry systems employ automatic, real-time range, logic, and missing value checks. Data sets will be cleaned, verified and archived, and then read into SAS (Enterprise Guide 4.1; SAS Institute, Cary, NC) data sets, which also will be archived. One official copy of all the study data and a master data dictionary will be maintained and updated regularly by the study data analyst. All analytic and tracking database files will be stored in a secure network drive with daily backups. One copy of the backups will be saved on-site and one off-site. Separate archival databases will be permanently maintained. The data files can be shared by authorized study personnel both on-site and in remote locations via a secure virtual private network. Data security will be ensured through password protection and data encryption.

Protected health information will be used and disclosed in accordance with the HIPAA regulations.

### Treatment Fidelity

Intervention quality assurance procedures ensure that project activities are standardized across the interventionists and across the cohorts and that intervention process data are collected accurately. To achieve this, standardized protocols, procedures, and educational materials are prepared, and staff are systematically trained in their use. Provider and auditor checklists are created to ensure that the intervention protocols are followed and that treatment objectives for each group session are met. Interventionists will complete a Provider Checklist after each session. All group and individual sessions will be audiotaped and a random sample of 10% selected for rating by a qualified individual using the Auditor Checklist. When a session is reviewed with less than 85% of treatment-specific objectives met, the auditor will inform the PI who will remediate interventionist training as needed. This process will continue through all treatment waves so that interventionist drift can be swiftly and consistently corrected.

## Discussion

On a population basis, the high prevalence of obesity among adults with asthma suggests an important opportunity to improve the lives of many such individuals. While the clinical treatment of asthma should continue to emphasize implementation of proven pharmacological and patient self-management strategies [22], the available evidence is already sufficient to warrant the investigation of including evidence-based weight loss strategies as an adjunct therapy for asthma patients who are also obese. Intensive weight loss interventions that employ a combination of recommended dietary, physical activity, and behavioral strategies have consistently resulted in weight losses in the range of 5-7%, which are associated with significantly reduced risk of well-recognized co-morbidities of obesity, such as diabetes and hypertension [57-60]. The efficacy of such a comprehensive, evidence-based, lifestyle approach to weight loss in improving asthma outcomes has not been investigated for obese individuals with asthma.

In BE WELL, the primary objective is to investigate whether weight loss, resulting from dietary modification, physical activity and behavior change, has significant clinical benefits for improving asthma control in obese adults. To our knowledge, BE WELL is the first study with adequate design and power for investigating the longitudinal effects of a behavioral weight loss intervention on asthma control. The only RCT for a similar purpose published to date was conducted by Stenius-Aarniala et al. [26] with the sample of 38 adult obese asthmatics. The results showed a net mean weight loss of 9.1%, which was associated with significant improvements in self-reported asthma symptoms and objectively assessed lung function (by spirometry) over 12 months. Other, non-randomized studies reported that weight loss induced by surgery [70-72] or dietary restriction [23,24,26,73] was associated with improved asthma symptoms, lung function, medication use, quality of life, and health care utilization.

The targeted clinical population in BE WELL is important from the standpoint of its risk for poor asthma outcomes, as well as metabolic and cardiovascular disease. For such individuals, weight loss through intensive lifestyle intervention, rather than surgical intervention or dietary restriction alone, is recommended as first-line therapy. Weight loss is recommended for obese patients with asthma by The National Asthma Education and Prevention Program Expert Panel Report 3 [22], but a lack of strong evidence of the efficacy of weight loss for improving asthma control was recognized by the Expert Panel. BE WELL will provide objective evidence on whether a state-of-the-art weight loss lifestyle intervention achieves a statistically and clinically meaningful improvement over a year's follow-up in asthma control and other manifestations that EPR3 considers indicative of current impairment (symptoms, lung function, rescue medication use, asthma-specific quality of life) and future risk (asthma exacerbations and medication side effects).

Achieving the goals of this study holds considerable potential for advancing the understanding of the causality of the obesity-asthma association and identifying effective behavioral approaches for the management of asthma in adults with comorbid obesity. This study will also serve as a foundation for future studies aimed at understanding the mechanisms by which weight loss is expected to improve asthma control, which may also illuminate the mechanism(s) linking obesity and the development of asthma. Future research is also needed to investigate the effect of weight loss on asthma control among children - a significantly under-researched area even compared to the limited research in adults [74]. Findings from this RCT, if as projected, will strengthen current guidelines for treating obese adults with asthma, which may lead to reduced morbidity and mortality related to both chronic diseases.
